**Figure 1 F1:**
[figure not shown]
Study design of the EQCP-trial on teamwork.

To enhance understanding on how the complex intervention, in case the care pathway, was actually implemented and under what conditions this implementation process was successful or not, the use of qualitative methods such as process evaluations alongside randomised controlled trials is advised [28]. This is because multiple behavioural and organisational factors will influence the extent in which the intervention can be integrated into everyday healthcare practice [29]. These factors will in turn determine their actual effectiveness. Therefore, the context in which the care pathway was developed and the implementation process will be evaluated using process measures during and after pathway-implementation in the intervention group.

### Inclusion and exclusion criteria

Inclusion on cluster level required the written agreement to participate from the hospital management, the medical head of the division, and the head nurse. In addition, they had to agree that they will not develop and implement a care pathway for COPD-exacerbation or PFF within the time frame of the study when randomised in the control group. Finally, the participating hospitals needed an expected volume of more than one hundred COPD-exacerbation or PFF patients annually. To have a comparable sample across all clusters, the following inclusion criteria on individual level are:

1. All professionals that according to the medical head of the division and head nurse are members of the interprofessional team caring for COPD-exacerbation or PFF patients from admission until discharge out of the acute hospital ward.

2. To be part of the interprofessional care team is further conceptualized as being part of the group of clinicians and staff who have a shared clinical purpose and direct care responsibilities for the respective patient group during the set time period.

3. All individual participants need to be member of the team during one specific week—chosen by the study coordinator and can be defined as an average week, with normal staff ratios—where patients are being followed for the two other trials of the EQCP project [23]; Because we want to study interprofessional teamwork, each cluster is asked to minimally include the orthopaedic surgeons/pneumologists, head nurse, nurses, physiotherapists, and social workers in their sample. Based on their own judgment, the medical head of the division, in consensus with the head nurse, can decide to include other professional groups in their sample.

4. In some hospitals COPD-exacerbation or PFF patients are being admitted at multiple nursing wards, *e.g.*, due to capacity problems or other organisational issues. If that is the case, then the clusters are asked to only include these team members that are working on the ward where the respective patient groups are being admitted most frequently.

Exclusion criteria are:

1. All team members that are not working (*e.g.*, on leave) during the chosen week.

2. All team members who are only temporarily part of the team (*e.g.*, student nurses in training).

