**Methods/design:**

An international post-test-only cluster Randomised Controlled Trial (cRCT), combined with process evaluations, will be performed in Belgium, Ireland, Italy, and Portugal. Teams caring for proximal femur fracture (PFF) patients and patients hospitalized with an exacerbation of chronic obstructive pulmonary disease (COPD) will be randomised into an intervention and control group. The intervention group will implement a care pathway for PFF or COPD containing three active components: a formative evaluation of the actual teams’ performance, a set of evidence-based key interventions, and a training in care pathway-development. The control group will provide usual care. A set of team input, process and output indicators will be used as effect measures. The main outcome indicator will be relational coordination. Next to these, process measures during and after pathway development will be used to evaluate the implementation processes. In total, 132 teams have agreed to participate, of which 68 were randomly assigned to the intervention group and 64 to the control group. Based on power analysis, a sample of 475 team members per arm is required. To analyze results, multilevel analysis will be performed.

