### Measures

The set of effect measures is described in Table 1. Teamwork is traditionally described using systems theory with an ‘input-process-output’ based approach [6]. This implies that effectiveness of teamwork is defined by a complex set of interactions between team inputs (context and structure of the team), team processes, and team outputs. Because we want to study the impact of care pathways on all facets of teamwork, we adopted this multifaceted ‘input-process-output’ approach in our choice of team indicators. The selection of measures is based on the international expert panel on relevant indicators to follow-up in care processes [32] and the systematic review of the relationship between care pathways and teamwork [12]. Hence, the research team made a substantiated decision on the measures based both on identified relevance to follow-up and expected effect of care pathways. As mentioned before, relational coordination is our primary effect measure. Next to the effect measures, a set of covariates will also be measured (Table 2). All team indicators will be analyzed on individual level, except for some team input indicators that will be measured on cluster level. These data will be collected with the use of both validated tools and structured questionnaires developed by the research team. The study coordinators will be trained in how all tools need to be completed. To guarantee anonymity, the team members will be asked to return the completed surveys to the study coordinators in a closed envelope. Afterward, these closed envelopes will be collected by a member of the research team.

**Table 1 T1:** Set of effect measures

**Effect measures**	**Typology**	**Level of analysis**	**Description**	**Instrument**	**Respondents**
Team composition	Team input	Cluster level	The different professional groups of which the team is built up of.	Team membership list	Study coordinator
Team reflexivity	Team input	Cluster level	Frequency of follow up of the care process.	Structured questionnaire	Study coordinator
Team meetings	Team input	Cluster level	Frequency of team meetings.	Structured questionnaire	Study coordinator
			Number of different professional groups attending team meetings.		
Leadership structure	Team input	Cluster level	Leadership structure of the team: No team leader/1 team leader/shared leadership	Structured questionnaire	Study coordinator

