One strength of the study is the use of a high-quality cRCT design with multilevel analysis, as required to evaluate complex interventions affecting groups of people [24]. Second, we include in our design a realistic evaluation approach by using process evaluations [28]. Third, we study the impact on teamwork in all its facets, using an input-process-output approach. Fourth, the choice of team indicators to follow-up is based on extensive literature review and international expert panel. Fifth, we set clear inclusion criteria for team members, which will enhance the comparability of our clusters. On the contrary, we did give the medical head of the division and head nurse the opportunity to choose additional professional groups that are also members of their team according to them, because ‘team composition’ is one of our team input indicators. Because we expect that the intervention teams will evaluate the composition of their team, our hypothesis is that they will be composed of more professional groups than the control teams. Sixth, the international nature of the study, and because we both include COPD teams (medicine) as PFF teams (surgery), increases generalisability. Finally, with the large number of participating teams, we should have enough power to find significant effects.

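### The five-group minimum for the survey sample can mask arm differences in team composition and leaves its hypothesis to optional groups listed by heads who know their allocation

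*Protocol article*

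**What the plan says.** Three places in the protocol article bear on this point.

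- **Inclusion and exclusion criteria.** Eligible individuals are "All professionals that according to the medical head of the division and head nurse are members of the interprofessional team" caring for these patients. The second criterion ties membership to direct responsibility for care, and the third ties it to one chosen week. The third criterion also sets a minimum for every cluster in either arm: "each cluster is asked to minimally include the orthopaedic surgeons/pneumologists, head nurse, nurses, physiotherapists, and social workers in their sample". It then adds that "the medical head of the division, in consensus with the head nurse, can decide to include other professional groups in their sample". The section gives comparability across clusters as the purpose of these criteria.
- **Measures, Table 1.** Team composition is a cluster-level effect measure of the team-input type, described as "The different professional groups of which the team is built up of". Its instrument is the "Team membership list", supplied by the study coordinator.
- **Discussion.** The heads were given "the opportunity to choose additional professional groups that are also members of their team according to them", and the reason stated is that team composition is one of the indicators. Of the intervention teams, the authors write that "our hypothesis is that they will be composed of more professional groups than the control teams".

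Study design adds that teams learned their allocation just before the intervention began, and that the arms are compared once, after about nine months, in a post-test-only design.

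**The concern.** A rule meant to make clusters alike feeds an outcome meant to show how they differ. If the membership list is drawn up under the sampling rule, two things follow.

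First, a team that in practice works without, say, a social worker or a physiotherapist may list one because it was asked to. A gap that a pathway might close would then not show in the control arm.

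Second, what can still differ between the arms is the number of optional groups. That number depends on whom the medical head and head nurse regard as members, and they know their allocation. Intervention teams are expected to have reconsidered their composition as part of the work, so they may list more widely even if the people giving care have not changed. The control arm has no baseline with which to separate a wider team from a wider list.

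At stake is the reading of one stated, directional hypothesis on a non-primary measure.

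**Working it through.** The plan gives no effect size, power or sample size for team composition. Its figures of 364 and 475 team members per arm concern relational coordination and play no part here. The check is therefore a reading of the sections together, followed by an illustration.

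**1. What the list records.** For one team, let C be the number of the five core groups it truly works with (0 to 5) and E the number of other groups it truly works with. True composition is C + E. If the team follows the request fully, and its heads list b groups more (or fewer) than the true optional ones, the list shows 5 + E + b.

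**2. Arm difference, intervention (I) minus control (K).**
- True: (C_I − C_K) + (E_I − E_K)
- Listed: (E_I − E_K) + (b_I − b_K)

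The core-group term drops out and a listing term enters. Nothing in the article bounds either one.

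**3. Size of the masking, by assumption.** Take C_I = 5, C_K = 3 and equal optional groups. The true difference is 2 and the listed difference is 5 − 5 = 0. More generally, suppose that a share p of control teams truly lacks one core group, no intervention team does, and all comply. The masked mean difference is then p groups: 0.1 for p = 10% and 0.5 for p = 50%. The article gives no value for p, and if p is zero nothing is masked.

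**4. Can the hypothesis be tested above the floor?** Clusters: "68 were randomly assigned to the intervention group and 64 to the control group". I simulated listed groups as 5 + Poisson(λ) in control teams and 5 + Poisson(λ + d) in intervention teams, with 4,000 replicates and a Kruskal-Wallis test at two-sided 0.05. The values of λ and d are my assumptions. Share of replicates significant:

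| λ (control mean of optional groups) | d = 0 | d = 0.5 | d = 1 |
|---|---|---|---|
| 0.5 | 0.055 | 0.894 | 1.000 |
| 1 | 0.048 | 0.692 | 0.994 |
| 2 | 0.054 | 0.455 | 0.948 |
| 3 | 0.046 | 0.321 | 0.841 |

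A common floor of five therefore does not prevent a test.

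**5. What the table does not show.** The simulation sees only what is listed. A shift of d = 0.5 that came wholly from listing habits (b_I − b_K = 0.5, no true change) would be significant equally often, about 0.32 to 0.89 of the time. Power to detect a difference in listing does not show that the listing measures composition.

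**The case against.** The strongest reply is that a floor is not a fixed list. The minimum is followed at once by freedom to add groups, with no upper limit, and the Discussion shows that the authors left this open because composition is an indicator. A reader might infer from the minimum alone that the inclusion rule fixes the outcome and that the hypothesis cannot be tested. The documents do not support that: more groups can appear above five, and step 4 shows that such a difference is detectable.

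Other objections also carry weight:

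- Clusters are asked, not obliged, to include the five groups. Read with the membership criteria, the request may mean only that these members should not be left out. Masking arises only where a team lists someone it would not otherwise count as a member. This stands as a condition, but the article does not say which rule gives way when a team truly lacks a core group.
- No sentence says that the membership list and the survey sample are the same list. That is inferred, although the Discussion itself links the eligibility rule to the composition indicator.
- The optional groups are described as team members in the heads' view, not merely as people chosen for a survey. That is correct, but the judgment remains local and unblinded.
- Table 1 also records how many professional groups attend team meetings, which the minimum does not touch. This is a useful cross-check, but it measures attendance rather than composition.
- Nothing suggests that control teams work with only three of the five groups. Agreed: that example is illustrative.

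**Conclusion.** The point holds as a limit on sensitivity and a possible reporting bias in one of the 16 effect measures in Table 1. The five-group request, combined with reading composition from the membership list, can mask arm differences in the core groups. It leaves the stated hypothesis to rest on optional groups whose listing is at the discretion of heads who know their allocation.

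The masked amount equals the true arm difference in core groups among teams that list to meet the request. It could be zero, and the article gives nothing from which to estimate it. The conclusion assumes that the list follows the sampling rule and that at least some teams comply by listing groups they do not really work with. The possible bias in the optional groups does not need that second assumption.

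The primary outcome, relational coordination, and its sample size are unaffected.

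**What to change.** Separate the two uses of the list.

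- Score team composition from a fixed yes/no checklist of professions, core groups included, in the structured questionnaire that study coordinators already complete. The wording should be identical in both arms and ask about actual participation in the care of these patients over a set period.
- Have the checklist completed before the survey list is drawn up, and change the instrument for team composition in Table 1 accordingly.
- Keep the five-group minimum as a rule for survey sampling only.

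The cost is one extra item. Composition will no longer match the list of people surveyed. The checklist is still a local report by someone who knows the allocation, so it removes the floor and narrows the room for discretion but does not blind the measure. The survey sample and the primary analysis do not change.

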### Sample size

In each of the four participating countries, hospitals were asked to participate by E-P-A in close cooperation with each national coordinator. In total, 132 teams (65 COPD teams and 67 PFF teams) agreed to participate (Figure 2). After the randomisation process, 68 teams were assigned to the intervention group (33 COPD teams and 35 PFF teams). Sixty-four teams were assigned to the control group (32 COPD teams and 32 PFF teams).

**Figure 2 F2:**
[figure not shown]
Participating teams in the EQCP-trial on teamwork.

Sample size calculation in a cRCT is based on the expected improvement in the main outcome parameter [24,30]. Our research team decided to use the team process indicator ‘relational coordination’ as main outcome parameter for the EQCP-trial on teamwork. The concept of relational coordination (RC) describes a mutually reinforcing process of communicating and relating for the purpose of task integration [31]. The following criteria justify our choice: RC describes communication and relations within the type of teams we are focusing on; an international panel of scientific experts and hospital managers identified team communication and relations as highly relevant for follow-up as team indicators (Content Validity Indexes of 89% and 86%, respectively) [32], and both are dimensions measured with the concept of RC; Gittell *et al.* showed that there is a clear mediating relationship between RC and the performance effects of care pathways [10]; and systematic literature review showed a positive relation between care pathways and both team communication and relations [12].

To calculate the expected improvement, existing data available through the formative evaluation (see below) of the 20 participating Belgian clusters randomised in the intervention arm were used. This set contains the scores on RC of 362 participating individual team members. RC is scored on a scale from 1 (low RC) to 5 (high RC). The range of the average RC-scores on cluster level in the dataset was 2.9 to 3.9. The gap between the highest and lowest score was thus 1.34. We then identified 4 as cut-off score, because this is the average between our top score (3.9) and the top score (4.2) in the nine-hospital study of Gittell *et al.*[31]. In our sample, 30% of participants (107/362) scored higher than 4. If we take this actual gap as expected improvement, then we can expect that the percentage of participants scoring more than 4 would increase to 40% after care pathway implementation (30%*1.34). Based on a power of 80% and a significance level of 0.05 (two-sized), we would need up to 364 team members per arm to observe a difference of 10% (case = 40%; control = 30%) in number of participants scoring higher than 4 on RC. Given an inflation factor (IFF = 1.306) using the ICC out of two previous cRCTs on pathway-effectiveness by Panella *et al.* (ICC = 0.018) and the average sample size of the Belgian clusters in the intervention group during the formative evaluation (n = 17) [33,34], the required sample size increased to 475 team members per arm. Considering the average sample size of 17 team members per cluster, we need 28 clusters per arm.

### The complex intervention: care pathway implementation in the intervention arm

The care pathway intervention contains three active components (Figure 3):

1. Formative evaluation of the teams’ performance before implementation: For this, a measure of the teams’ performance on team indicators and on patient process indicators is planned. The set of team indicators that will be used for this evaluation is described below. The patient process indicators are described in the research protocols of the other two EQCP trials [35,36]. These process indicators measure the teams’ compliance to the key interventions in the care process. Key interventions are those that, based on evidence-based medicine, need to be performed to guarantee high-quality care, and that thus will have significant impact on patient outcomes. An evaluation of performance to these process indicators will be performed for 20 consecutive patients. Each team will receive a feedback report with their own results, both on team and on patient level, benchmarked with the results of the other participating teams. Furthermore, a workshop per country will be organised on the interpretation of these results and on how these results should be presented to the teams. These workshops will be lead by an organizational psychologist ([name]) and experts in care pathway development ([name] and [name]). All involved study coordinators will be invited. After a general introduction, the participants will be divided in small groups of five to help them interpret the results. The formative evaluation will help the teams to understand their actual performance, their points for improvement, and their actual level of organisation of the care process.

2. Evidence-based key interventions: Each team will receive a set of evidence-based key interventions for COPD-exacerbation or PFF. This set is based on an extensive literature review, Map of Medicine® (http://www.mapofmedicine.com), and on consensus by international clinical experts using a Delphi survey. The key interventions and outcomes include both in-hospital interventions and information for a safe discharge. A workshop will be organised on the content and evidence base of these interventions. These workshops will be lead by clinical experts in COPD and PFF. Next to the study coordinator, three key stakeholders of the participating teams will be invited. A teach-the-teacher based approach will be used.

3. Training in pathway development: Each study coordinator will be trained to develop the care pathway based on the findings of the formative evaluation. In the training workshop, a care pathway implementation protocol based on the Deming Plan-Do-Study-Act cycle and behavioural change strategies, which is generally accepted as the standard method for care pathway implementation, will be used (Figure 4) [37]. These one-day workshops will be led by experts in pathway development ([name] and [name]) and organizational and team change ([name]). Again, a teach-the-teacher based approach will be used. Change will be further supported by giving the possibility to exchange best experiences among participating teams.

**Figure 3 F3:**
[figure not shown]
Active components of the EQCP-complex intervention.

**Figure 4 F4:**
[figure not shown]
Care pathway implementation protocol based on the Deming-PlanDoStudyAct cycle.

### Measures

The set of effect measures is described in Table 1. Teamwork is traditionally described using systems theory with an ‘input-process-output’ based approach [6]. This implies that effectiveness of teamwork is defined by a complex set of interactions between team inputs (context and structure of the team), team processes, and team outputs. Because we want to study the impact of care pathways on all facets of teamwork, we adopted this multifaceted ‘input-process-output’ approach in our choice of team indicators. The selection of measures is based on the international expert panel on relevant indicators to follow-up in care processes [32] and the systematic review of the relationship between care pathways and teamwork [12]. Hence, the research team made a substantiated decision on the measures based both on identified relevance to follow-up and expected effect of care pathways. As mentioned before, relational coordination is our primary effect measure. Next to the effect measures, a set of covariates will also be measured (Table 2). All team indicators will be analyzed on individual level, except for some team input indicators that will be measured on cluster level. These data will be collected with the use of both validated tools and structured questionnaires developed by the research team. The study coordinators will be trained in how all tools need to be completed. To guarantee anonymity, the team members will be asked to return the completed surveys to the study coordinators in a closed envelope. Afterward, these closed envelopes will be collected by a member of the research team.

**Table 1 T1:** Set of effect measures

**Effect measures**	**Typology**	**Level of analysis**	**Description**	**Instrument**	**Respondents**
Team composition	Team input	Cluster level	The different professional groups of which the team is built up of.	Team membership list	Study coordinator
Team reflexivity	Team input	Cluster level	Frequency of follow up of the care process.	Structured questionnaire	Study coordinator
Team meetings	Team input	Cluster level	Frequency of team meetings.	Structured questionnaire	Study coordinator
			Number of different professional groups attending team meetings.		
Leadership structure	Team input	Cluster level	Leadership structure of the team: No team leader/1 team leader/shared leadership	Structured questionnaire	Study coordinator
Coordinating mechanisms	Team input	Cluster level	Use of guidelines and protocols, information systems, case management, interdisciplinary patient rounds, and interdisciplinary team meetings.	Structured questionnaire	Study coordinator
Dedicated team members	Team input	Individual level	If team members are exclusively dedicated to COPD of PFF care within the team or not.	Structured questionnaire	Team members
Perceived ‘teamness’	Team input	Individual level	To what extent is the team perceived by the team members as being a real interprofessional team?	Structured questionnaire (score 1–5)	Team members
Work environment	Team input	Individual level	To what extent is the work environment supportive for teamwork?	Structured questionnaire (score 1–5)	Team members
Management support	Team input	Individual level	To what extent is the hospital management supportive for teamwork?	Structured questionnaire (score 1–5)	Team members
Conflict management	Team process	Individual level	The quality of how conflicts are managed within the team.	Structured questionnaire (score 1–5)	Team members
Leadership quality	Team process	Individual level	Quality of leadership: general satisfaction with leader, leadership skills and effectiveness of leadership.	Structured questionnaire (score 1–5)	Team members
Team involvement	Team process	Individual level	How involved does each team member feel with the team?	Structured questionnaire (score 1–5)	Team members
Team climate for innovation	Team process	Individual level	- Team Vision: clarity of and commitment to objectives (4 items)	Team Climate Inventory[38]	Team members
			- Participative safety (4 items)		
			- Task orientation: emphasis on quality (3 items)		
			- Support for innovation (3 items)		
Relational coordination	Team process	Individual level	- Communication dimensions (4 items): frequent, timely, accurate and problem solving communication	Relational Coordination Survey[31]	Team members
			- Relationship dimensions (3 items): shared goals, shared knowledge and mutual respect		
Level of organised care	Team output	Individual level	Level of organisation of the care process:	Care Process Self Evaluation Tool[39]	Team members
			- Patient focused organisation (6 items)		
			- Coordination of CP (7 items)		
			- Communication with patient and family (4 items)		
			- Collaboration with primary care (3 items)		
			- Follow up of CP (9 items)		
Work Engagement	Team output	Individual level	Level of engagement to work:	Burn Out Inventory[40]	Team members
			- Emotional exhaustion (5 items)		
			- Mental detachment (5 items)		
			- Level of competence (5 items)		

**Table 2 T2:** Set of covariates

**Covariates**	**Level of analysis**	**Description**	**Instrument**	**Respondents**
Randomisation group	Cluster level	Group in which the team was randomised.	Structured questionnaire	Study coordinator
Patient group	Cluster level	Patient group for which the care pathway is being developed.	Structured questionnaire	Study coordinator
Team size	Cluster level	Number of individuals in the team.	Team membership list	Study coordinator
Hospital characteristics	Cluster level	- Number of beds	Structured questionnaire	Study coordinator
		- Patient volume		
		- Teaching status		
		- Dedicated ward or not		
Team tenure	Cluster level	Average number of years that the team members are part of the team.	Structured questionnaire	Team members
Individual characteristics of the team member	Individual level	- Age and gender	Structured questionnaire	Team members
		- Professional group of team member		
		- % of working time		
		- Years of experience with the patient group		
		- Years of being a team member		
		- Has the team member a leading role within the team		

The process measures that will be used in the intervention group are described in Table 3. First, to measure the level of adherence to the complex intervention, the study coordinator will have to score to what extent the evidence-based key interventions were actually implemented. Second, to evaluate the implementation process, process follow-up files will be administered to the study coordinators at several time points during and after implementation. Furthermore, semi-structured interviews with key stakeholders of each cluster will be performed after implementation. We are planning to interview representatives of three groups of stakeholders: the study coordinator, hospital management, and key stakeholders of the interprofessional team. For each of these groups, a specific interview guide will be developed. Considering the large international sample, to enhance feasibility, the interviews will only be performed in a selection of clusters.

**Table 3 T3:** Set of process measures

**Process measures**	**Typology**	**Description**	**Instrument**	**Respondents**
Adherence to the complex intervention	Implementation parameter	Process adherence parameter measuring the extent to which the evidence-based key interventions were actually implemented.	Process-follow-up files	Study coordinator
Project team composition	Implementation parameter	The composition of the project team: size and professional groups that are part of it.	Process-follow-up files	Study coordinator
Project satisfaction	Implementation parameter	Satisfaction with the implementation process.	Process-follow-up files	Study coordinator
Project meetings	Implementation parameter	Number of meetings the project team organised during the implementation process.	Process-follow-up files	Study coordinator
Facilitators and barriers	Implementation parameter	What facilitators and barriers were encountered during the implementation process of the care pathway?	Semi-structured interviews	Study coordinator and stakeholders of the management and team
Pathway effectiveness	Implementation parameter	How did the implementation of the care pathway affect patient care and teamwork?	Semi-structured interviews	Study coordinator and stakeholders of the management and team

